### Sample size

The study was powered to have at least 80% power to detect based on a two-sided test with alpha equal to 0.05 a difference of 10 points in general health-related quality of life measured with the EORTC QLQ-C30 (primary outcome) between both groups at the primary endpoint, i.e., 6 months post-diagnosis. A drop-out of 5%, 10%, and 20% is anticipated at 6 weeks, 12 weeks, and 6 months, respectively. Based on reference values for the EORTC QLQ-C30, a standard deviation of 22.7 was assumed [49]. Further, moderate correlations equal to 0.5 were assumed for the associations with the baseline measurement. Under these assumptions, 75 subjects per group are necessary. The study was also powered on one key-secondary outcome, i.e., the physical functioning subscale of the EORTC QLQ-C30. Since the assumed standard deviation for this subscale was slightly lower (based on the EORTC QLQ-C30 reference values 2008), this has no impact on the required sample size. Otherwise said, with 75 subjects per group, the power is higher than 80% for this secondary outcome, more specific 87.7%.

For the feasibility study, no sample size calculation was performed.

### Data analysis

#### Effectiveness study

For the general health-related quality of life and the key-secondary outcome (physical functioning subscale), the mean value at 6 months will be compared between both groups after correction for the baseline value. To handle the presence of missing data, this ANCOVA approach will be implemented using a constrained longitudinal data analysis (cLDA) using all collected measurements over time (baseline, 6 weeks, 12 weeks, 6 months, 12 months). Both comparisons will be based on a two-sided test with alpha equal to 0.05.

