### Trial design

A parallel, two-arm, open label trial will be conducted. This single center prospective randomized clinical study will be performed to investigate the effectiveness and the feasibility of a comprehensive supervised exercise program (CSEP) in addition to usual supportive care compared to usual supportive care alone in patients undergoing CRT for HNC, the EffEx-HN trial. This is a superiority trial design because we aim to investigate whether a CSEP is more effective in improving health-related quality of life than the current standard of supportive care. To study the feasibility of the CSEP, a qualitative study will be performed in a subgroup of participants of the large prospective randomized clinical study described above. Quantitative data on feasibility will be collected in all participants.

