### Eligibility criteria

HNC patients are eligible to participate if they are scheduled for radiotherapy at the Radiation-Oncology department of the University Hospitals Leuven. Inclusion criteria are as follows: (1) ≥ 18 years, (2) diagnosed with primary malignant tumor head and neck region, (3) ECOG performance score 0–1, (4) able to complete baseline assessments prior to start of (chemo)radiotherapy, (5) physically and mentally capable of taking part in an exercise program and motivated to engage in a supervised exercise program. Patients are excluded if one of the following exclusion criteria are present: (1) < 18 years, (2) ECOG performance score ≥ 2, (3) treated with palliative intent, (4) evidence of distant metastases, (5) no basic level of reading and writing in Dutch. Participation of a patient in the study can be discontinued based on the participant’s request or if the disease is worsening, to the extent that exclusion criteria are present (treatment with palliative intent, evidence of distant metastases).

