### Allocation and randomization

A 4-size permuted block randomization is used. The randomization is computer-generated, in particular the allocation to the intervention or the control group is concealed and performed by the randomization module of the Research Electronic Data Capture system (REDCap) before the start of the exercise program, ensuring blinding of the research team [16, 17]. The sequence of randomization is decided by the patient’s record identifier in REDCap, which is received after signing informed consent. An open label study is performed, which means that the therapist/assessor and patients are not masked for the allocation to the intervention or control group. The therapist giving the exercise program and the assessor are the same individual during the entire study period.

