### Outcomes

#### Effectiveness study

At 5 time-points, evaluation moments are organized, during which self-reported questionnaires and clinical assessments are performed. The evaluation moments take place at baseline (T0), at 6 weeks (T1), at 12 weeks (T2), at 6 months (T3), and at 12 months (T4). The assessments will be performed at the Department Physical Medicine at the University Hospitals Leuven. Most of the questionnaires are conducted at home, through a digital link to the Research Electronic Data Capture (REDCap). The evaluation moments take place in the hospital. In total, administering the questionnaires through REDCap takes 60 min. The clinical assessment takes 45 to 60 min. The primary outcome parameter is health-related QOL measured with the European Organisation for Research and Treatment of Cancer quality of life questionnaire (EORTC QLQ-C30) at 6 months post-diagnosis. A key-secondary outcome is the physical functioning subscale of the EORTC QLQ-C30. The secondary outcome measures are also shown in Tables 2 and  3. In addition, personal factors, including patient-related factors (age, social status, work status), and cancer (treatment)-related factors will be collected from the participant’s medical file.

**Table 2 Tab2:** Study outcome measures by assessment time-point: self-reported outcomes

Domain	Questionnaire	*T*_0_	*T*_1_	*T*_2_	*T*_3_	*T*_4_

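### The primary and key-secondary models are stated with adjustment for the baseline score alone; prespecifying planned treatment would be a cheap gain in precision, and the two descriptions of the population should be reconciled

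*Protocol article*

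**What the plan says.** **Analysis.** Under Data analysis, Effectiveness study, the article states for general quality of life and for the physical functioning subscale that "the mean value at 6 months will be compared between both groups after correction for the baseline value". It does this with a cLDA over all five visits, at a two-sided alpha of 0.05. The baseline value is the only adjustment named.

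**Randomisation.** Under Allocation and randomization: "A 4-size permuted block randomization is used". The sequence follows the REDCap record identifier. No stratification factor is named there or in the abstract.

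**Population.** Trial design describes the comparison as "compared to usual supportive care alone in patients undergoing CRT for HNC", and the section on the exercise programme also times its start from CRT. Under Eligibility criteria, "HNC patients are eligible to participate if they are scheduled for radiotherapy", and the inclusion criterion on baseline assessments puts the chemotherapy part in brackets as optional. Surgery is neither required nor excluded there. Surgery followed by radiotherapy, with or without chemotherapy, appears only in Background and rationale, as a usual route for locally advanced disease.

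**Data.** Under Outcomes, Effectiveness study, "cancer (treatment)-related factors will be collected" from the medical file. Data security and management adds age, gender, diagnosis and TNM stage.

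**Sample size.** The effect to be detected is "a difference of 10 points in general health-related quality of life measured with the EORTC QLQ-C30", assessed at 6 months, with a target of at least 80% power and a two-sided alpha of 0.05. Also, "a standard deviation of 22.7 was assumed", with a correlation of 0.5 with baseline, 20% drop-out at 6 months and 75 subjects per group.

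**The concern.** Patients treated with radiotherapy alone and patients treated with chemoradiotherapy may have different quality of life 6 months after diagnosis. The baseline score can carry only part of that difference. Whether it is taken before radiotherapy (Eligibility criteria) or within a week of its start (Table 1), it cannot record toxicity still to come.

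If planned treatment predicts the outcome beyond baseline and is left out of the model, its effect stays in the residual variance. The standard error is then larger than it needs to be, in a trial sized to just reach 80% power.

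There is also a missing-data argument. The article expects 20% drop-out by 6 months and relies on cLDA to handle it. If planned treatment influences both drop-out and later quality of life, a model without it makes missing at random harder to defend.

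Finally, if the report describes CRT patients but the enrolled group includes patients on radiotherapy alone, the conclusion will not match the sample.

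**Working it through.** **Inputs from the Sample size section:** difference 10 points, SD 22.7, correlation with baseline 0.5, two-sided alpha 0.05, power at least 80%, 20% drop-out at 6 months, 75 per group.

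**Step 1: reproduce the planned sample size.**
- SD after baseline adjustment: 22.7 × √(1 − 0.5²) = 19.66.
- Completers per arm by simple ANCOVA: 2 × [19.66 × (1.960 + 0.842) / 10]² = 60.67, so 61. Then 61 / 0.80 = 76.25, so 77 per arm (75.8 if the unrounded figure is carried through). This is within 2 of the stated 75.
- Power with 75 × 0.80 = 60 completers per arm: the standard error is 19.66 × √(2/60) = 3.59, and Φ(10/3.59 − 1.96) = 79.6%.
- Under cLDA with a common baseline mean, monotone drop-out of 5%, 10% and 20%, and all pairwise correlations 0.5 (an assumption; the article gives only the correlation with baseline), 75 per arm gives a standard error of 3.55 and power of 80.5%. With 74 per arm, power is 79.98%.

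So 75 is the smallest group size that reaches 80% under the planned model. The stated figure is right and has almost no reserve.

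**Step 2: what a further covariate could add.** Let R² be the share of the variance remaining after baseline that planned treatment explains. The documents give no value, so this is an assumption shown over a range. The adjusted SD becomes 19.66 × √(1 − R²), and power is Φ(10 / [SD × √(2/60)] − 1.96).

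| Assumed R² | Adjusted SD | Power, 60 completers per arm |
|---|---|---|
| 0 | 19.66 | 79.6% |
| 0.02 | 19.46 | 80.4% |
| 0.05 | 19.16 | 81.6% |
| 0.10 | 18.65 | 83.6% |

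These are completers-only ANCOVA figures, and cLDA starts slightly higher (80.5%). Read the increments, 0.8 to 4.0 percentage points, rather than the crossing of 80%.

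To put the range in context: a binary factor held by a share p of patients that shifts the outcome by 10 points (both assumed) contributes variance 10² × p(1 − p). That is 21 at p = 0.30 and 25 at p = 0.50. Against 19.66² = 386.5, these are 5.4% and 6.5%, provided the baseline score carries none of it. Any overlap with baseline lowers them.

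**Step 3: chance imbalance without stratification.** With 75 per arm, the SD of the between-arm difference in a proportion is √(2p(1 − p)/75).
- p = 0.30: 0.075, so a 95% range of ±15 percentage points. With a 10-point effect, the contrast moves by up to about 1.5 points.
- p = 0.50: 0.082, so ±16 percentage points and about 1.6 points.

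Both are 95% limits, to be set against a standard error of 3.55. That standard error already contains this variation.

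**The case against.** The strongest reply is that nothing stated is wrong. Under randomisation, a baseline-adjusted cLDA is unbiased and keeps its error rate without treatment in the model, and it reaches the stated power. This stands. A reader might infer from unequal treatment mix that the primary contrast is biased, or from 79.6% that the trial is underpowered. Neither follows. Chance imbalance is already counted in the standard error, and 79.6% comes from a completers-only calculation that is not the planned analysis.

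Second, this is a condensed article. A reader might infer that randomisation is definitely unstratified, or that baseline is deliberately the only covariate. The article does not say either: it names no stratification factor and no further covariate, and an analysis plan that is not shown could add covariates. This stands in part. The Data analysis section nevertheless goes beyond general intent, giving the contrast, the adjustment, the model and alpha, so it is fair to suggest an improvement to the model as stated.

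Third, the gain cannot be sized from the documents. Prevalence, prognostic strength and variance explained are all assumed, and the baseline score may already carry part of the effect. This stands, and the gain could be zero.

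Fourth, a reader might infer that post-operative patients are enrolled. The eligibility criteria do not mention surgery, and the background mention does not establish it. If such patients are enrolled, their baseline, taken around the start of radiotherapy, may already reflect the operation.

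Fifth, a three-level factor with a separate effect at each of five visits would add 2 × 5 = 10 parameters, and a rare category would be unstable. This is a reason to keep the factor simple, not to leave it out.

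**Conclusion.** The point holds as an efficiency improvement and a wording inconsistency, not as an error in the analysis. The planned model is valid and meets its target at about 80.5% power, assuming all between-visit correlations are 0.5, but with a margin of about one patient per arm. Adding planned treatment would gain roughly 0.8 to 4.0 percentage points of power if it explains 2% to 10% of the residual variance, and nothing if it adds nothing beyond baseline. It would also strengthen the missing-at-random assumption if treatment is related to drop-out. The mismatch between CRT in Trial design and radiotherapy in Eligibility criteria is in the text whatever an analysis plan may say.

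**What to change.** 1. In the primary and key-secondary cLDA, prespecify planned treatment as known at randomisation: at least chemotherapy yes or no, with sparse categories collapsed by a rule set in advance. Let its effect vary by visit. Use the plan at randomisation, not the treatment eventually received. Fix this before outcome data are examined, since a covariate added later would be open to challenge as post hoc.
2. Confirm that planned treatment is recorded as it stood at randomisation. The article says treatment factors are collected but not in what form.
3. State whether randomisation was stratified and, if so, by what.
4. Reconcile Trial design with Eligibility criteria so that the conclusion matches the enrolled population, and say explicitly whether post-operative patients are included.

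Cost: a binary factor with an effect at each of five visits adds 1 × 5 = 5 parameters in a trial of 150 patients. Treatment-related data are already being collected, so beyond the check in item 2 the change is one of wording.

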#### Feasibility study

All video recorded interviews will be transcribed verbatim. Transcripts (audio and typed feedback) will be uploaded into NVivo 12 coding software. Framework matrix analysis will categorize themes, which will yield specific, recurring information regarding patient feedback [48].

### Trial monitoring

Regarding quality assurance, assessments and interventions will be performed by an experienced physical therapist, [name], with a master’s degree in rehabilitation sciences. The physical therapist and PI have a GCP certificate. Besides, the PI and UZ Leuven will permit trial-related monitoring, audits, EC review, and regulatory inspections (where appropriate) by providing direct access to source data and other documents.

## Discussion

The clinical trial is ongoing. The recruitment started in January 2022. There are no practical or operational issues involved in performing the study.

### Trial status

This is version 2.2 of the protocol, written on January 20, 2022. The recruitment started in January 26 2022, directly after approval of the Ethics Committee. The approximate date when recruitment will be completed is estimated at the end of 2024.

## Data Availability

The study will be conducted in compliance with the principles of the Declaration of Helsinki (2008) and the principles of Good Clinical Practice and in accordance with all applicable regulatory requirements. The investigator and the participating site shall treat all information and data relating to the study disclosed to the participating site or investigator in this study as confidential and shall not disclose such information to any third parties or use the information for any purpose other than the performance of the study. The collection, processing, and disclosure of personal data, such as patient health and medical information, are subject to compliance with applicable personal data protection and the processing of personal data (European General Data Protection Regulation (GDPR) and the Belgian Law of July 30, 2018, on the protection of natural persons with regard to the processing of personal data). The investigator and the participating site will protect the data from disclosure outside the research according to the terms of the research protocol. Any data required to support the protocol can be supplied on request. The datasets analyzed during the current study and statistical code can be made available by the corresponding author on reasonable request, as the full protocol.

## Abbreviations

EffEx-HN: Effect of exercise in head and neck cancer patients
RCT: Randomized controlled trial
CSEP: Comprehensive supervised exercise program
HNC: Head and neck cancer
CRT: Chemoradiotherapy
QOL: Quality of life
ICF: International Classification of Functioning, Disability and Health
IG: Intervention group
PI: Principal investigator
REDCap: Research Electronic Data Capture system
BPI: Brief Pain Inventory
PROMIS-PF-SF: PROMIS physical function short form
LSIDS-H&N: Lymphedema Symptom Intensity and Distress Survey-Truncal and Head and Neck
FACIT-F: Functional Assessment of Chronic Illness Therapy—fatigue scale
DASS-21: Depression, Anxiety and Stress Scale-21
GSES: General Self-Efficacy Scale
PACE: Patient-Centered Assessment and Counseling for Exercise
IPAQ: International Physical Activity Questionnaire
QuickDASH: Short version of the Disability of Arm, Shoulder and Hand
IPA: Impact on Participation and Autonomy
PAR-Q: Physical Activity Readiness Questionnaire
BREQ-2: Behavioral Regulation in Exercise Questionnaire 2
BMI: Body mass index
ECW: Extracellular water
SMI: Skeletal muscle index
CTC: Common Toxicity Criteria
1RM: One repetition maximum
cLDA: Constrained longitudinal data analysis
ICF: Informed consent form
